### Aims and Hypotheses

The EMERALD study, detailed below, aims to examine (1) the effect of intervention exposure on HIV and STI risk behaviors (eg, drug use and unprotected sex) and HIV and STI cumulative incidence over time in FSWs in the intervention group compared with those in the comparison group, (2) how sociostructural (eg, social cohesion and stigma) and structural vulnerability (eg, financial and housing stability) indicators change and are associated with the biological and behavioral outcomes over time in FSWs in the intervention group compared with those in the comparison group, (3) the role of these indicators as mediators of the intervention effect on study outcomes, and (4) the implementation of the intervention through qualitative (eg, in-depth interviews) and quantitative (eg, assessment of program fit, reach, and cost, and facilitators and barriers to utilization measures).

The SPARC center and associated outreach is the intervention being evaluated by the EMERALD study, which consists of an 18-month longitudinal cohort study comprising intervention (n=224) and control (n=161) participants, a cross-sectional survey to assess program reach (n=100), and in-depth interviews (n=45) to assess SPARC implementation. We hypothesize that addressing structural drivers and more immediate medical needs, in combination with peer outreach, will lead to community empowerment and reduce FSWs’ HIV and STI incidence and behavioral risks.

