#### Cohort Study Target Population and Sample

Cohort participants were FSWs aged ≥18 years who live in Baltimore City; self-reported that they had traded sex for money, goods, or drugs 3 or more times in the past 3 months; and were not currently enrolled in our previous cohort study, the SAPPHIRE study [40]. Although transgender female sex workers (TFSWs) who reported being assigned male at birth were encouraged to visit the SPARC center and engage with peer outreach workers, they were excluded from the EMERALD study cohort because of a lack of comparable recruitment locations between the intervention and control areas.

Participants were assigned to a study arm based on the geographic location in which they were recruited. The initial target sample size was 350 women based on power calculations to observe a change in the intervention compared with the control group over the 3 follow-up visits. The assumptions used for the calculation were (1) n=200 in the intervention group and n=150 in the comparison group, (2) lost-to-follow-up (LTFU) rate of 10% to 20% in the intervention (effective n=160-180) and LTFU of 20% to 25% in the comparison group (effective n of 120-112), (3) intraperson correlation (Rho)=0.2-0.4, (4) varying levels of baseline risk behavior rate, and (5) a 2-sided α=.05. Thus, assuming effective sample sizes of n=160 in the intervention and n=112 in the comparison groups, the power is 83% to detect an odds ratio of 0.50, assuming a 20% prevalence rate of a risk behavior (eg, drug use) in the control group and an intraperson correlation of Rho=0.2. For the cumulative incidence outcome, with an average N contributing to the analysis of 170 in the intervention and 120 in the control groups, and assuming annual incidence rate of 6%, the power is 80% to detect a rate ratio of 0.28.

The enrollment target was increased to 450 midway through data collection after power calculations were reassessed based on actual retention rates within the sample, which were closer to 65%. The LTFU rate was higher than anticipated based on previous studies [41], likely because of high incarceration rates, the mobility of the population, and the length of time between study visits (6 months). Although we aimed for a sample of 450 participants, recruitment was stopped at 385 because of reaching saturation in the recruitment areas and repeatedly encountering participants attempting to reenroll in the study.

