### Limitations

Despite successful implementation and the novelty of this intervention in a US setting, we encountered several challenges throughout this study. Although TFSWs experience disproportionately high rates of victimization and are underrepresented in research, a lack of comparable recruitment locations in the intervention and control areas prohibited the inclusion of TFSWs in our study [63,64]. In addition, the onset of the COVID-19 pandemic in March 2020 required adaptations to service provision and data collection. In-person services at the SPARC center were stopped on March 17, 2020. However, because the framework was already in place, the SPARC team was able to quickly pivot to an all-outreach service model when the COVID-19 pandemic forced the closure of the drop-in center.

Regarding the EMERALD evaluation, data collection for the cross-sectional survey was paused at the onset of the COVID-19 pandemic, and data collection was shifted to a telephone format for the remaining 18-month surveys. As a result, we were unable to conduct HIV and STI testing for 27 participants. We plan to reopen in-person services at the SPARC center, resume the 96 in-person cross-sectional surveys, and complete the 19 remaining in-depth interviews when data collection with human subjects is deemed safe and appropriate.

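### Power of 83% and 80% is printed for the initial target and not restated for the 385 women enrolled at about 65% retention, and the 80% for incidence does not follow from its printed inputs over 18 months

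*Protocol article*

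**What the plan says.** All the power statements are in the protocol article, section Cohort Study Target Population and Sample. The initial target of 350 assumes "n=200 in the intervention group and n=150 in the comparison group" and "a 2-sided α=.05". Loss to follow-up is put at a "rate of 10% to 20% in the intervention (effective n=160-180") and at 20% to 25% in the comparison group (effective 120 to 112).

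Two powers follow:
- **Behavior:** 83% for an odds ratio of 0.50, with effective n of 160 and 112, 20% control prevalence and Rho=0.2.
- **Incidence:** 80% for a rate ratio of 0.28 at 6% per year, "with an average N contributing to the analysis of 170 in the intervention and 120 in the control groups". This sentence gives no follow-up length and no formula.

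The next paragraph says that "power calculations were reassessed based on actual retention rates within the sample, which were closer to 65" percent, and that the target was raised to 450. It continues: "Although we aimed for a sample of 450 participants, recruitment was stopped at 385". Aims and Hypotheses describes an "18-month longitudinal cohort study comprising intervention (n=224) and control (n=161) participants". Limitations adds, for the 18-month visits moved to telephone, that "we were unable to conduct HIV and STI testing for 27 participants". No power or detectable effect is printed for the sample obtained.

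**The concern.** The printed powers rest on retention of 75% to 85%: 160/200 = 80% and 112/150 = 75% for behavior, 170/200 = 85% and 120/150 = 80% for incidence. The article itself reports about 65%. Enrolling 385 instead of 350 makes up part of that loss, but the sponsor's own reassessment asked for 450. A reader who meets a null result will weigh it against 83% and 80%, the only figures on the page. For incidence, a primary biological endpoint with few expected events, that would make a null result look more informative than it is.

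**Working it through.** **Effective sample.** 0.65 x 224 = 146 and 0.65 x 161 = 105; 0.65 x 385 = 250. The planned totals were 160 + 112 = 272 and 170 + 120 = 290. At 65% retention these need 272/0.65 = 418 and 290/0.65 = 446 enrolled. 450 x 0.65 = 292 fits an aim of restoring 290, but the article does not say so.

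**Behavior.** An odds ratio of 0.50 from p0 = 0.20 gives odds of 0.25 x 0.50 = 0.125, so p1 = 0.125/1.125 = 0.111. Averaging three follow-up visits multiplies the variance by (1 + 2 x Rho)/3, which is 0.467 at Rho=0.2 and 0.600 at Rho=0.4. Each n is divided by that factor and entered in a two-sided 5% comparison of two proportions (unpooled, pooled and log-odds versions).

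| Sample | Rho=0.2 | Rho=0.4 |
|---|---|---|
| Planned 160/112 | 82-84% | 72-74% |
| 146/105 | 79-81% | 69-71% |

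The printed 83% reproduces. Like for like, the loss is about 3 points at either Rho.

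**Incidence at the planned sample.** I take 6% as the control rate and 18 months as the follow-up (both assumptions, since the sentence states neither).
- Expected events: control 120 x 0.06 x 1.5 = 10.8; intervention 170 x 0.06 x 0.28 x 1.5 = 4.28.
- Log rate ratio: |ln 0.28| = 1.273; SE = sqrt(1/10.8 + 1/4.28) = 0.571; power = Phi(1.273/0.571 - 1.960) = Phi(0.27) = 61%.
- Two proportions, 9.0% against 2.52%, pooled variance under the null: 67%.

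The printed 80% does not reproduce. An event-count (Schoenfeld) formula gives 68%. One-sided tests give 72-79%. About 80% appears only with 24 months of follow-up (two proportions 79.6%, Schoenfeld 80.3%).

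**Incidence at other samples, same inputs.**

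| Average N | Log rate ratio | Two proportions |
|---|---|---|
| 170/120 (planned) | 61% | 67% |
| 146/105 (65% at every visit) | 54% | 61% |
| 185/133 (65% at 18 months, linear loss) | 65% | 71% |

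The last row uses mean retention (1 + 0.65)/2 = 0.825: 0.825 x 224 = 185 and 0.825 x 161 = 133. By two proportions, the step from the printed 80% to 67% exists before any retention problem (13 points); the step from 67% to 61% is the retention effect (6 points).

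**The case against.** **The text already ties the figures to the initial target.** It does, and it discloses the retention, the reassessment and the stop at 385. The article misreports nothing here. Statistical Analysis also offers power details on request. That stands as mitigation, but the offer does not correct the printed figures, and the reassessed power appears nowhere.

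**The visit behind the 65% is not named.** A reader might infer that the effective sample is simply 250 and that neither printed power is met. The documents do not establish that. The 65% was seen midway through data collection, women who miss a visit may return, and those lost contribute time at risk up to their last visit. With linear loss to 65% at 18 months, retention at the three follow-up visits averages (88% + 77% + 65%)/3 = 77%, or about 172/123. That exceeds 160/112, so the behavioral shortfall disappears, as does the retention part of the incidence shortfall (185/133 against 170/120).

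**Three tempting figures are not supported.**
- Rescaling the printed 80% to 146/105 gives Phi(2.802 x sqrt(0.868) - 1.960) = 74%. That carries forward a starting value that does not reproduce.
- Setting 69-71% at Rho=0.4 against the printed 83% mixes two values of Rho; the planned sample already gives 72-74% at Rho=0.4.
- Removing the 27 untested women altogether ignores their earlier tests; they lose only the 18-month one.

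**The 6% may mean something else.** Read as the average over both arms at 170/120, the control rate is 0.06 x 290/(120 + 0.28 x 170) = 10.4% per year, and power over 18 months is 84-89%. That does not reproduce 80% either, but the error then runs the other way. At the 13.7% per year that the Background reports for chlamydia in the earlier cohort, 146/105 would give about 88-94%. The incidence result is therefore conditional on 6% as the control rate.

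**Conclusion.** The point holds as a failure to restate power, together with an incidence figure that its printed inputs do not support.
- **Behavior:** a loss of about 3 points if 65% applies at each visit in both arms, to 79-81% at Rho=0.2; no loss if 65% is the 18-month value with linear loss.
- **Incidence:** about 54-61% under the first reading and 65-71% under the second, against 80% printed. Even the planned 170/120 gives only 61-67%, so retention is the smaller part of the gap.

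The incidence figures assume a control rate of 6% per year, a rate ratio of 0.28, a two-sided 5% test and 18 months of follow-up. None of the calculations allows for correlation within the 10 recruitment areas, which the analysis models and which would lower power further by an amount the documents do not let one compute.

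**What to change.** In the sample-size paragraphs:
1. Keep 83% and 80% only as original design values for 350 women.
2. Recompute the incidence power from its inputs. Either correct the 80% or state the follow-up length, the formula and the arm to which the 6% refers.
3. Add power, or the minimum detectable odds ratio and rate ratio, for 224/161 at observed retention by visit and arm, over Rho 0.2-0.4. For incidence, count only visits with a test, so that the 27 women lose the 18-month test alone.
4. Interpret null results by confidence intervals, not by the printed powers.

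Do not print 74% as the replacement for 80%, and do not present the Rho=0.4 figure as a loss caused by retention. No further enrollment is proposed. All visit windows have closed, so the retention data should already be held; the cost is a short recalculation and some wording, and the downside is a less favorable stated power.

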#### Cohort Recruitment

EMERALD recruitment began 2 months before the opening of the SPARC center and took place from September 2017 to January 2019. The recruitment strategy for the EMERALD cohort was informed by SAPPHIRE, an earlier prospective cohort study of FSWs in Baltimore, conducted by this study team, which used targeted sampling [50]. Given that recruitment for SAPPHIRE concluded approximately 9 months before the launch of the EMERALD study, we conducted a series of geospatial analyses of possible sex work activity indicators using publicly available data [51] (eg, prostitution charge data and 911 call center reports of suspected prostitution) to understand possible shifts in the geotemporal distribution of sex work throughout Baltimore City (as compared with where we previously recruited FSWs in SAPPHIRE).

In total, the sampling frame for EMERALD consisted of 10 small geographic areas with high concentrations of sex work activity. Among them, 6 were located in the intervention area and 4 in the control area. Compared with our previous targeted sampling recruitment strategy among FSWs in Baltimore City [50], the time and day components of the sampling frame were selected based on analyses of time signatures associated with relevant secondary data in each location with high concentrations of sex work activity and supplemented with additional insights gleaned from SAPPHIRE. Before launching recruitment, staff conducted windshield tours in each location to confirm the presence of sex work activity.

A recreational vehicle (RV) retrofitted with 2 private interview areas and a bathroom for sample collection was driven to the field locations in the intervention and control areas 3 to 5 days per week depending on the interview volume. Each shift lasted approximately 4 hours at the recruitment site and was staffed by 1 field supervisor and 2 interviewers. A community advisory board made up of current and former sex workers provided input on all data collection strategies and instruments.

Potential participants were discreetly approached by staff who provided a brief description of the study. Due to the sensitive nature of sex work, drug use, and HIV, study staff were trained to refer to the study as a women’s health study when communicating with potential participants or community members. Women who were interested in participating were offered screening in a private area on the study RV. FSWs who were eligible and interested in participating in the study were asked to provide written informed consent for all study procedures using an electronic consent form. Following the consent process, participants completed a standard locator form, which included mobile and home phone numbers, addresses, social media usernames, places frequented by the participant, and contact information of family or friends. This locator information is collected and updated at every visit to increase the likelihood of successful retention for future study visits [41].

After completing the locator form, participants received HIV pretest counseling from trained staff and were tested for HIV using the OraQuick *ADVANCE* Rapid HIV-1/2 Antibody Test, which detects HIV-1 and HIV-2 antibodies in saliva in 20 minutes. While waiting for the results of their HIV test, participants completed a 45- to 60-minute audio-enhanced computer-assisted self-interviewing (A-CASI) survey, with staff on hand to provide assistance. The use of A-CASI provided uniformity of delivery and afforded greater privacy and confidentiality than an interviewer-administered survey, considering the sensitive nature of some survey questions. The baseline survey assessed sociodemographic characteristics, arrest and prison history, sex work history, frequency and type of police encounters, drug and sexual-risk behaviors, overdose and drug treatment history, general health history, experiences of sexual and physical violence, FSW social cohesion, stigma, empowerment, health service utilization, and a brief screening for posttraumatic stress disorder and depression symptoms (Table 1).

**Table 1 table1:** Variables reflected in the conceptual framework and collected as part of the EMERALD (Enabling Mobilization, Empowerment, Risk Reduction, and Lasting Dignity) study of female sex workers in Baltimore, Maryland.

Variable		Example question
**Outcomes and impact**		
	HIV diagnosis	N/A^a^
	Sexually transmitted infection diagnosis	N/A
	Substance use	Have you (injected, smoked, swallowed, or snorted—asked separately) any of the following drugs? Powdered cocaine Crack cocaine Heroin Fentanyl Buprenorphine or suboxone Prescription pain relievers Sedatives or tranquilizers Stimulants
	Condom use	In the last week, how often did you use condoms when having (vaginal or anal) sex with (clients or intimate partner)? Always Most of the time Sometimes Rarely Never Did not have (vaginal or anal) sex
	Safe drug use practices	In the last 6 months, did you use any of the following items that you know have been used by someone else? Syringes or needles Cookers Cotton None of these
**Confounders**		
	**Housing stability**	
		Have you been homeless in the past 6 months?
		Where do you currently stay? Place that you own Place that you rent Family member’s place Shelter Transitional housing program Hotel or motel Streets, park, car, or abandoned building
	**Financial stability**	
		In the past 6 months, did you depend on anyone financially? This includes for food or a place to stay.
		Do you currently owe money to anyone, including a person, company, or a bank?
	**Access to physical and mental health services**	
		Was there a time in the past 6 months when you wanted or needed to see a doctor or health care provider (other than addiction services) but could not?
	**Social cohesion**	
		You can count on other people who sell sex if you need to borrow money; 4-point Likert scale (strongly disagree to strongly agree)
		You look out for new girls when they start selling sex on the street; 4-point Likert scale (strongly disagree to strongly agree)
	**Collective action and social participation**	
		Do you participate in any of the following: Church Clubs Cultural activities Community organizations
	**Gender equity**	
		Men’s opinions are more important than women’s in making important decisions in a primary relationship; 4-point Likert scale (strongly disagree to strongly agree)
		If a man wants to have sex in a primary relationship and a woman does not, she should have sex to please him; 4-point Likert scale (strongly disagree to strongly agree)
	**Violent experiences [52]**	
		Thinking about your (clients or intimate partners): Have you been hit, punched, slapped, or otherwise physically hurt by them? Have they removed a condom during sex after agreeing to use one?
	**Sex work stigma [53]**	
		There are times you feel ashamed of selling sex; 4-point Likert scale (totally disagree to total agree)
		People’s attitudes about selling sex make you feel worse about yourself; 4-point Likert scale (totally disagree to total agree)
	**Empowerment [54]**	
		I have little control over the things that happen to me; 5-point Likert scale (totally disagree to total agree)
		There is little I can do to change many of the important things in my life; 5-point Likert scale (totally disagree to total agree)

^a^N/A: not applicable.

On completion of the survey, participants were asked to self-collect vaginal swabs with Aptima vaginal swabs (Hologic Inc) using the private RV bathroom. The samples were sent to the Baltimore City Health Department lab, which conducted nucleic acid amplification testing for gonorrhea and chlamydia. Once samples were collected, the participants received the results of their HIV test and posttest counseling. A 2-week appointment was scheduled to receive the STI test results.

Participants were given a US $70 prepaid Visa debit card as compensation for their time and offered relevant referrals to health and social services. Participants recruited from the intervention area were encouraged to visit SPARC and offered hygiene products such as sanitizer wipes and lip balm with SPARC branding, including the address and phone number of the center. Control area FSWs were offered similar EMERALD-branded items and provided neighborhood-specific referrals if requested but were not encouraged to visit SPARC.

#### Cohort Retention Methods

Follow-up visits for EMERALD occurred at 6, 12, and 18 months after the initial baseline interview. Participants received US $40 prepaid Visa debit cards for completing each follow-up visit. Participants were eligible to complete each follow-up visit 1 month before their actual interview date until 1 month after, for a total eligibility window of 2 months. Those who failed to complete an interview within the allotted eligibility window were considered lost to follow-up. Participants who missed a visit could still complete their next scheduled visit and were not withdrawn from the study.

Retention protocols were modeled after strategies used in SAPPHIRE [50] and are more fully described in a study by Silberzahn et al [41]. Briefly, retention strategies consisted of the aforementioned locator forms (eg, phone numbers, addresses, and social media accounts); promotional materials (eg, hand sanitizer, wipes, lip balm, and silicon bracelets) branded with the study logo and phone number; monitoring public information databases to determine if participants were incarcerated, had moved, or were deceased; and outreach in the form of phone calls, social media messaging, home visits, and repeated visits to recruitment areas in both the study RV and a study sedan, which was used for follow-up. The study team also relied on tracking teams of 2 study staff who were assigned participants to focus on with 1 month of eligibility remaining.

Building on the strategies used in SAPPHIRE, the EMERALD cohort retention protocols were enhanced using several additional strategies. A password-protected database was developed to monitor follow-up and participant progress during the study visits. Using this database, study management could easily determine current and projected follow-up rates, the number of participants due for a study visit (6, 12, and 18 months), and all previous contact attempts used to locate a participant. Field staff documented how participants were located (eg, phone calls and home visits) and time spent on van shifts and tracking, which allowed study management to determine adequate staffing and consider the best follow-up strategies. For example, study staff could monitor the number of difficult-to-reach participants due for follow-up surveys in specific study areas and direct tracking teams to these locations to increase the probability of chance encounters with participants. Additionally, check-in locator visits were conducted in between formal study visits at 3, 9, and 15 months to touch base with participants and inquire about any changes to contact information on file (eg, phone numbers, addresses, family and friends). Finally, although SPARC staff were prohibited from discussing the EMERALD study with clients, participants could obtain the EMERALD study phone number from SPARC center administrative staff at their request and use the SPARC office phone to contact the EMERALD study staff, determine follow-up eligibility, and schedule follow-up interviews.

